### Statistical analysis

2.7

#### Analysis of clinical outcomes

2.7.1

Analysis of clinical data (CARS, GSRS, SRS, ABC) will be conducted using SPSS 26.0. Continuous variables will be expressed as mean ± standard deviation. For comparisons between baseline and specific follow-up points, paired *t*-tests or Wilcoxon signed-rank tests will be used, as appropriate based on data distribution. To analyze the longitudinal changes in primary and secondary outcomes over the multiple time points, linear mixed-effects models will be employed to account for intra-subject correlations.

To ensure the highest standard of statistical analysis, we have formally engaged a qualified statistician as a consultant for this study. The statistician will be involved in the final data analysis plan, execution, and interpretation of results.

The primary analysis of clinical outcomes will be conducted on the per-protocol (PP) population, defined as all participants who complete the primary endpoint assessment at 12 months. A secondary analysis will be performed on the intent-to-treat (ITT) population, which includes all enrolled participants who have received at least one Fecal Microbiota Transplantation administration. For longitudinal data (e.g., GSRS), linear mixed-effects models are inherently robust to data missing at random. For missing primary endpoint data (e.g., 12-month CARS), multiple imputation techniques will be explored and applied if necessary, under the guidance of our study statistician.

#### Analysis of microbiota data

2.7.2

All microbiota-related statistical analyses will be conducted within R 4.5.1 (48).

Diversity Analysis: To calculate for both taxonomic and functional profiles to assess changes in community richness, evenness, and structure across different time points of FMT, diversity analysis will be conducted with the R package vegan version 2.7–2 (49) Alpha diversity (within-sample diversity, such as the Shannon index and Simpson index) and beta diversity (between-sample diversity, e.g., Bray-Curtis dissimilarity) will be calculated.

Differential Abundance Analysis: To identify taxa and functional pathways that exhibit significant changes, linear discriminate analysis with effect size (LEfSe) analysis (50) will be used with microeco package Version 1.15. 0 (51). After that, to identify associations between microbiota profiling and clinical improvements in core ASD symptoms or GI comorbidities (scores of ABC, CARS, SRS and GSRS), multivariate association with linear models (MaAsLin) analysis will be performed by Maaslin2 package Version 1.22.0 (52), followed by Benjamini-Hochberg correction for multiple hypothesis tests (53).

Statistical analysis (Microbiota): To determine differential abundance of metagenomic features, normality and homogeneity tests on all data will be conducted firstly. Measurement data such will be expressed as mean ± SE for normally distributed data and as median (P25, P75) for nonnormally distributed data. For normally distributed data with homogeneous variances in 2-group comparisons, paired *t*-tests will be used. Nonnormally distributed or nonhomogeneous data will be analyzed using nonparametric Wilcoxon tests. In multiple group comparisons, normally distributed data with homogeneous variances will be analyzed with analysis of variance, while nonnormally distributed or nonhomogeneous data will be analyzed with nonparametric Kruskal–Wallis tests (54). Correlations will be calculated between clinical and metagenomic features with Spearman's correlation. *P*-values will be adjusted with false discovery rate (FDR) with the method from Benjamini-Hochberg (53) when multiple hypotheses are considered simultaneously and will be denoted adj. P. All graphs will be visualized using the ggplot2 package (Version 4.0.0) (55).

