#### Secondary objectives

2.1.2

2.1.2.1 To analyze changes in gut microbiota composition during FMT treatment in children with ASD.

2.1.2.2 To explore correlations between core microbiota and clinical outcomes.

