### Study design

2.2

This is a prospective, open-label, single-arm, single-center clinical study enrolling children aged 2–12 years with moderate-to-severe ASD. The study aims to evaluate the efficacy and safety of FMT in ASD, investigate microbial colonization patterns, and identify core microbiota post-FMT. Findings will provide evidence-based support for clinical protocols and theoretical foundations for individualized precision therapy in ASD. A technical route map for the study is shown in Figure 1. All clinical data will be recorded on standardized Case Report Forms (CRFs) and entered into a secure, password-protected electronic database to ensure data quality and integrity.

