### Outcome measures

2.5

The schedule for all assessments is detailed in Table 1.

**Table 1 T1:** Visit schedule.

Time Window	Within 1 month pre-FMT (Baseline)	FMT treatment period*	1 week post-FMT	2 weeks post-FMT	3 weeks post-FMT	4 weeks post-FMT (±3 days)	5 weeks post-FMT (±3 days)	6 weeks post-FMT (±3 days)***	3 months post-FMT (±3 days)	6 months post-FMT (±3 days)	9 months post-FMT (±3 days)	12 months post-FMT (±3 days)***
Informed Consent	√											
General Data Collection	√	√										
Medical History Collection	√											
Vital Signs, Height, Weight	√	√	√	√	√	√	√	√	√	√	√	√
Inclusion/Exclusion Criteria	√											
Lab Tests**	√	√						√				√
Adverse Event Documentation		√	√	√	√	√	√	√	√	√	√	√
GSRS, DSR	√	√	√	√	√	√	√	√	√	√	√	√
CARS, SRS, ABC	√								√	√	√	√
Recipient Fecal Collection	√	√	√	√		√			√	√	√	√
Donor Fecal Collection	√											

* FMT treatment period: Includes 3 FMT administrations on Day 1, Day 3, and Day 5.

** Lab tests: Baseline tests include routine blood, urine, and stool tests, liver function (ALT, AST), renal function (BUN, Creatinine), coagulation profile, and ECG. Follow-up labs at 6 and 12 months will monitor long-term safety, including: (1) Immune/Inflammatory parameters (CBC with differential, hs-CRP, ESR) and (2) Metabolic parameters (Fasting Glucose, HbA1c, Fasting Lipid Profile, Liver Function Panel, Renal Function Panel).

*** Long-term safety & efficacy follow-ups will specifically monitor long-term safety, including immune, metabolic, and neurodevelopmental parameters.

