### Sample size calculation

2.8

The sample size for this prospective single-arm study was determined based on the primary outcome of the change in the CARS score from baseline to 12 months post-intervention. The calculation is based on the 12-month follow-up data from a large-scale preliminary study by Ye et al. (2022) on FMT for children with ASD (31).

In that study, the mean CARS score in children with ASD before treatment was 35.2 ± 6.5. Following FMT, the mean score at 12 months post-treatment was 31.0 ± 6.7. This represents a mean reduction (δ) of 4.2 points, which is considered the clinically significant difference to be detected in this protocol.

The standard deviation of the difference (*σd*) is required for the calculation. Assuming a conservative correlation coefficient (*r*) of 0.5 between baseline and 6-month measurements (a common assumption for pre-post study designs), the standard deviation of the difference can be estimated using the formula:$$\sigma_{d}=\sqrt{\sigma_{\;pre}^{2}+\sigma_{\;post}^{2}-2r\sigma_{\;pre}\sigma_{\;post}}$$This yields an estimated *σd* of approximately 6.60.

Using a two-sided paired *t*-test, with a significance level (*α*) of 0.05 and a desired statistical power (1-*β*) of 80% $\left(Z_{\beta }=0.8416\right)$, the required sample size (*n*) was calculated using the following formula: $n=(Z_{\alpha /2}+Z_{\beta }{)}^{2}\sigma_{d}^{2}/\delta^{2}$.Therefore, *n* = [(1.96 + 0.8416)^2^ × 6.60^2^]/(4.2^2^) ≈ 19.4.

Based on these parameters, the minimum required sample size is calculated to be 20 participants.

To account for a potential dropout rate of approximately 20% during the 6-month follow-up period, the sample size needs to be adjusted.

Adjusted sample size = *n*/(1—dropout rate) = 20/(1–0.20) = 25.

Therefore, the planned enrollment of 30 participants is more than sufficientto provide adequate statistical power for evaluating the primary outcome of this study.

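### For three or more stool visits, section 2.7.2 names tests for independent groups although the samples are serial within child, so the multi-visit microbiota tests are too conservative

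*Protocol article*

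**What the plan says.** Section 2.2 describes the design: "This is a prospective, open-label, single-arm, single-center clinical study enrolling children aged 2–12 years with moderate-to-severe ASD". There is no control arm, and the Discussion notes the absence of healthy controls. The first secondary objective (2.1.2.1) reads "To analyze changes in gut microbiota composition during FMT treatment in children with ASD". In Table 1 (section 2.5) the row "Recipient Fecal Collection" is ticked in nine windows: baseline, the FMT period, weeks 1, 2 and 4, and months 3, 6, 9 and 12.

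Section 2.7.2 gives the diversity analysis the task of assessing change over the time points of FMT. For features that change it names "linear discriminate analysis with effect size (LEfSe) analysis", followed by MaAsLin2 for associations with clinical scores. Its general rules are:

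- two groups: paired t-test if normal with equal variances, otherwise a Wilcoxon test;
- several groups: analysis of variance if normal with equal variances; otherwise, "nonnormally distributed or nonhomogeneous data will be analyzed with nonparametric Kruskal–Wallis tests".

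For the clinical scores, section 2.7.1 states that "linear mixed-effects models will be employed to account for intra-subject correlations". Section 2.7.2 has no matching statement and names no repeated-measures ANOVA, Friedman test, blocking or random effect for child.

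**The concern.** In a single-arm trial whose stated microbiota comparison is between time points, the groups in section 2.7.2 are occasions in the same children. The section itself treats them so by pairing the t-test when there are two. With three or more occasions the pairing disappears. Kruskal–Wallis has no repeated-measures form, and nothing indicates that the analysis of variance is a repeated-measures one. LEfSe, as the method is generally known, screens features with the same kind of unpaired rank test; the protocol does not describe its steps.

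This is a named test that does not fit the data, not a detail left for later. At stake is the sensitivity of the multi-visit tests for objective 2.1.2.1: a change present in most children can be hidden behind stable differences between them. Benjamini-Hochberg adjustment does not repair this, because it starts from p-values that are already too large.

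**Working it through.** **The plan's own figure.** The protocol gives no power or error rate for the microbiota analyses. Its only calculation (section 2.8, CARS) reproduces: σd = √(6.5² + 6.7² − 2 × 0.5 × 6.5 × 6.7) = 6.60; n = (1.96 + 0.8416)² × 6.60² / 4.2² = 19.4, so 20, and 20 / 0.80 = 25. It has no bearing on this point.

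**Inputs from the protocol.** 30 children (2.8); nine stool windows (Table 1). The nominal two-sided level of 0.05 is the one used in 2.8.

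**Assumptions.** The within-child correlation ρ of a microbiota feature is not given, so it is varied from 0.2 to 0.7; the 0.5 in section 2.8 is for CARS only. Data are normal with equal correlation between all visits of a child. The shift is 0.6 SD at every post-baseline sample. No samples are missing.

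**Why the direction is conservative.** With variance σ² at each visit and no true change, the mean square between visits has expectation σ²(1 − ρ). The one-way error mean square pools the variances within visits and has expectation σ². The F ratio is therefore centred near 1 − ρ instead of 1: about 0.8 at ρ = 0.2 and 0.3 at ρ = 0.7. Kruskal–Wallis behaves in the same way on ranks. A repeated-measures test uses σ²(1 − ρ) as its error and is centred near 1.

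**Simulation, 30 children × 9 samples, 0.6 SD shift.**

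| ρ (assumed) | Kruskal–Wallis power | Friedman power |
|---|---|---|
| 0.2 | 42% | 57% |
| 0.3 | 39% | 63% |
| 0.5 | 28% | 82% |
| 0.7 | 16% | 97% |

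With no shift, Kruskal–Wallis rejects in 1.3% of runs at ρ = 0.2, falling to about 0% at ρ = 0.7. Friedman rejects in about 4% to 5% throughout.

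**Other settings.**

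- A 0.5 SD shift, 30 children, ρ = 0.3 / 0.5 / 0.7: Kruskal–Wallis 21% / 12% / 4%, Friedman 46% / 62% / 87%. One-way ANOVA gives 24% / 13% / 6%, repeated-measures ANOVA 55% / 72% / 93%. The loss is therefore not peculiar to the rank test.
- Section 2.8 inflates the sample "To account for a potential dropout rate of approximately 20% during the 6-month follow-up period". With 30 × 0.80 = 24 children and a 0.5 SD shift: Kruskal–Wallis 15% / 7% / 3%, Friedman 35% / 48% / 77%. The pattern is the same.
- At ρ = 0, Kruskal–Wallis holds its level (5.0%) and loses nothing. The problem comes entirely from the within-child correlation.

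**The planned paired test in the same 0.6 SD setting.** For one follow-up visit against baseline, the SD of the difference is √(2(1 − ρ)). At ρ = 0.5 this is 1.0, so the noncentrality is 0.6 × √30 = 3.29 and simulated power is about 88%. Over ρ = 0.2 to 0.7 the paired t-test has about 73% to 98%.

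**The case against.** **The paired comparisons are already planned.** At these settings a paired t-test of one visit against baseline detects the shift with about 73% to 98% power. This stands. A reader might infer that real engraftment changes will be missed by the trial as a whole; the protocol does not support that, because the loss sits in the multi-visit tests. For non-normal data this relief requires that Wilcoxon means the signed-rank test. Section 2.7.2 does not say which, but its paired t-test suggests it.

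**False positives.** A reader might also infer that spurious links between taxa and scores will be reported. For comparisons between time points the error is purely conservative. Inflation would arise only if correlations treated several visits of one child as independent. The sentence beginning "Correlations will be calculated between clinical and metagenomic features with" does not say that visits are pooled, and the neighbouring MaAsLin sentence speaks of clinical improvement, which fits one change per child. If the five visits with both CARS and stool were pooled, a nominal 5% Spearman test with no true link would reject in about 9%, 15% and 24% of runs at ρ = 0.3, 0.5 and 0.7 in both variables. That is a conditional risk, not something the plan states.

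**Other readings of the section.** Kruskal–Wallis and LEfSe would suit comparisons between different children, such as GSRS responders against non-responders (2.5.1). Section 2.7.2 names no such grouping; the comparison it names is across time points. Analysis of variance is not called one-way, so a repeated-measures reading is open for it, but not for Kruskal–Wallis. The mixed-model sentence in 2.7.1 refers to primary and secondary outcomes, and microbiota is a secondary outcome. However, that section opens with the four clinical scales in SPSS, while 2.7.2 places all microbiota analyses in R with its own list of tests, so the sentence does not clearly reach them.

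**Size.** The gap depends on ρ and is modest at low values (42% against 57% at 0.2). The simulated data are normal, where the section would choose analysis of variance; the one-way ANOVA results show the same loss.

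**Conclusion.** The point holds, limited to comparisons over three or more visits. Kruskal–Wallis, analysis of variance if one-way, and LEfSe without blocking by child ignore that the samples are serial. At a 0.6 SD shift the cost in Kruskal–Wallis power against Friedman is about 15 percentage points at ρ = 0.2 (57 − 42), 24 at 0.3 (63 − 39), 54 at 0.5 (82 − 28) and 81 at 0.7 (97 − 16). Actual type I error is about 1% or less instead of about 5%. These sizes rest on an assumed correlation, normal data with equal correlation between visits, and complete sampling; the direction holds for any positive correlation of this form. No separate figure was derived for LEfSe.

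The consequence is limited to the multi-visit tests for secondary objective 2.1.2.1 in a trial that calls itself exploratory. The CARS and GSRS analyses are untouched. It is still worth correcting before analysis, because the protocol already uses suitable methods elsewhere.

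**What to change.** In section 2.7.2:

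- For comparisons over three or more visits, replace analysis of variance and Kruskal–Wallis by a mixed model with child as random effect, as in 2.7.1, or by repeated-measures ANOVA or Friedman. The mixed model is preferable where visits are missing, since Friedman needs complete sets.
- For change over time in taxa and pathways, use MaAsLin2, which is already planned, with visit as fixed effect, child as random effect and Benjamini-Hochberg control. Keep LEfSe as descriptive only.
- If correlations or MaAsLin2 associations with clinical scores use more than one visit per child, include a child effect or use one change score per child.

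The cost is analysis code and wording. No new data, visits or children are needed.

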
However, FMT's clinical application remains contentious:
**Inconsistent Efficacy:** A randomized controlled trial (RCT) found no significant difference between oral FMT capsules and placebo, potentially due to donor variability or administration routes (30).**Safety Concerns:** Although most adverse effects (AEs) are mild to moderate, risks such as infections and long-term safety in ASD patients require further evaluation (31, 32).**Unclear Mechanisms:** While FMT alters gut microbiota composition in ASD, the pathways linking microbial changes to symptom improvement (e.g., specific metabolites or immune pathways) remain undefined, hindering biomarker-guided personalized therapy (33).**Uncertain Long-term Outcomes:** Long-term follow-up studies report diminishing therapeutic effects over time, with partial relapse of core symptoms in some patients (31).The complexity of ASD demands interdisciplinary collaboration. As a powerful tool to modulate the MGBA, FMT holds promise for addressing neurodevelopmental deficits at their root. Despite current limitations, advancements in mechanistic understanding, technological innovation, and clinical standardization may position FMT as a cornerstone of precision medicine for ASD, offering new hope for affected children and families. Future efforts must balance scientific rigor with clinical translation to bridge the gap between laboratory research and real-world therapeutic applications. Therefore, we hypothesize that multi-course FMT will significantly improve both GI symptoms and core behavioral deficits in children with moderate-to-severe ASD, and that these clinical improvements will be associated with the restoration of gut microbial diversity and function.

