#### Control of confounding variables

2.4.5

To minimize known confounding factors that can influence the gut microbiota, legal guardians will be instructed to maintain the child's typical diet and to avoid introducing major dietary changes (e.g., starting a gluten-free/casein-free diet) during the study period. A baseline 3-day dietary log will be collected. All concomitant medications and the use of supplements will be recorded at each study visit. While household environment cannot be controlled, data on significant dietary patterns and concomitant medications will be collected and considered as potential covariates in exploratory statistical models.

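### The microbiota–clinical association tests in section 2.7.2 are not tied to within-child change; if visits are pooled, a shared shift after FMT can pass for a link with CARS

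*Protocol article*

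**What the plan says.** The Introduction ends with a hypothesis about improvement: that "these clinical improvements will be associated with the restoration of gut microbial diversity and function". Section 2.1.2 turns this into a secondary objective: "To explore correlations between core microbiota and clinical outcomes".

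Section 2.7.2 names two tests for it:

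- Spearman: "Correlations will be calculated between clinical and metagenomic features with Spearman's correlation". No visit, change score or handling of repeated samples is given.
- Maaslin2, used "to identify associations between microbiota profiling and clinical improvements in core ASD symptoms or GI comorbidities (scores of ABC, CARS, SRS and GSRS"). The text says that "multivariate association with linear models (MaAsLin) analysis will be performed by Maaslin2 package" but names no fixed or random effects.

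Benjamini-Hochberg adjustment follows. Section 2.7.1 names mixed models for within-subject correlation, but for the clinical scales only. Section 2.4.5 says that diet and concomitant medication will be "considered as potential covariates in exploratory statistical models"; visit is not mentioned. The design has no control arm: "This is a prospective, open-label, single-arm, single-center clinical study enrolling children aged 2–12 years with moderate-to-severe ASD". Table 1 schedules recipient stool together with CARS, SRS and ABC at baseline and at 3, 6, 9 and 12 months.

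**The concern.** The hypothesis says that children whose microbiota changes more should improve more. A correlation of levels asks something else.

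In a single-arm trial all children pass from before to after FMT together. Features shift because donor material was given. Scores may fall for several reasons, and the Discussion concedes that placebo effects and natural progression cannot be excluded. When baseline and follow-up values are pooled, that common step alone correlates the two, and no control arm exists to expose it. A random child intercept does not remove the step, because it lies within each child.

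At stake is the mechanistic conclusion: features reported as linked to improvement could simply be those that moved after FMT. Multiplicity adjustment does not help, because the p-values entering it are not valid for a child-level link.

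**Working it through.** **The plan's own figures.** Section 2.8 gives CARS 35.2 ± 6.5 before and 31.0 ± 6.7 at 12 months, with r = 0.5.

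- σd = √(6.5² + 6.7² − 2·0.5·6.5·6.7) = √(42.25 + 44.89 − 43.55) = √43.59 = 6.60.
- n = (1.96 + 0.8416)² × 43.59 / 4.2² = 19.4, rounded up to 20; 20/0.80 = 25.

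The plan's figures reproduce and are not in dispute. They supply the CARS inputs below.

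**Inputs.** From the protocol: CARS SD (6.5, or 6.5 and 6.7), fall 4.2, within-child correlation 0.5, five shared visits, N = 30 planned, and 30 × 0.80 = 24 after dropout. Assumed: the fall is present at all follow-ups (section 2.8 gives it at 12 months only); a feature shifts by 0.5 to 1.5 SD after FMT; the feature's within-child correlation is 0.5; and feature and CARS are independent at child level.

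**Size of the artefact.** With one baseline visit in five, a common step adds −s·d·(1/5)(4/5) = −0.16·s·d to the covariance, in SD units. For s = 1 and d = 4.2/6.5 = 0.646 this is −0.103. The variances become 1 + 0.16 = 1.16 and 1 + 0.16 × 0.646² = 1.067. The pooled correlation is therefore −0.103/√(1.16 × 1.067) ≈ −0.09, with no child-level link. The simulated mean Spearman coefficient is also −0.09.

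**Rejection rates, five visits pooled, unadjusted two-sided 5%, no child-level link** (Spearman 3,000 replicates, mixed model 400):

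| Feature shift (SD) | Spearman, N=24 | Spearman, N=30 | Random intercept, no visit, N=24 | Same, N=30 |
|---|---|---|---|---|
| 0 | 14.3% | 14.4% | 5.8% | 4.5% |
| 0.5 | 19.0% | 17.3% | 17.8% | 20.8% |
| 1.0 | 23.1% | 26.5% | 41.0% | 47.8% |
| 1.5 | 31.6% | 36.7% | 61.8% | 72.2% |

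A repeat of the mixed-model simulation reached 75% at the top end. With 400 replicates the standard error near 72% is √(0.72 × 0.28/400) ≈ 2.2 points, so the two runs agree.

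The zero-shift row separates two problems. Spearman already rejects in 14% to 15% there, because repeated samples are treated as independent. The mixed model handles that dependence and sits near 5%, so its rise in the lower rows comes from the common step alone.

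**Alternatives, same settings.**

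- Spearman on baseline-to-12-month changes: 4.4% to 5.7%.
- Visit and child means both removed: 4.6% to 5.7%.
- Random intercept plus visit as a fixed effect: 4.2% to 7.2%.
- Visit means removed but children ignored: 16% to 17%, so a visit term alone is not enough.
- Spearman at a single visit: 4.8% to 5.5% at N = 30.

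**Single visit and improvement.** If stable child traits correlate at 0.5 to 0.8 but changes are unlinked, single-visit Spearman at 12 months rejects in 19% to 53% of trials. Those are correct rejections of its own null. They show that the test responds to stable differences between children, not to improvement.

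**The case against.** The strongest reply is that section 2.7.2 never says that raw values are used or that visits are pooled. The Maaslin2 sentence is aimed at improvement, and its parenthesis may only name the instruments. Model terms usually sit in an analysis plan, and section 2.7.1 mentions a final plan involving a statistician. The objective speaks of clinical outcomes, for which a correlation of levels is a legitimate exploratory answer.

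Much of this stands. A reader might infer that the protocol prescribes raw-on-raw analysis, or that any feature that shifts will be tied to any score that falls. The documents support neither: the first reads silence as a statement, and the second turns a raised probability, dependent on assumed shifts, into a certainty. Nor may the whole pooled Spearman rate be blamed on the common step, since 14% to 15% is present without it.

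What does not stand is that this is only omitted detail. Read literally, the Spearman sentence means levels pooled over visits or levels at one visit, and neither tests the hypothesis in the Introduction. Nor does the section handle repeated samples elsewhere: for multiple-group comparisons it names analysis of variance and Kruskal–Wallis, with no repeated-measures form.

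**Conclusion.** The point holds as a mismatch between hypothesis and named tests, with a conditional error rate. If the five shared visits are pooled, false links with CARS arise in about 17% to 37% of trials with Spearman and about 18% to 75% with a random-intercept model without visit. These rates rest on the assumed feature shifts of 0.5 to 1.5 SD and a 4.2-point fall at all follow-ups. If one visit is used, the error rate is nominal when no child-level link exists, but the question answered is not improvement. The matter is confined to a secondary, exploratory objective. It deserves correction because these results are meant to inform later controlled trials.

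**What to change.** In section 2.7.2, state that Spearman's correlation relates each child's change from baseline in the feature to that child's change from baseline in the score at the same visit.

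For Maaslin2, specify visit as a categorical fixed effect, child as a random effect, and the score split into the child's mean and the deviation from it. Test the within-child coefficient. Splitting into baseline and change instead leaves the error above 5% when stable traits correlate; centring on the child's mean with a visit term holds about 5%. Apply Benjamini-Hochberg to these p-values.

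The cost is a few sentences and extra model terms in software already named. No new data are needed, since stool and scores are already paired at baseline, 3, 6, 9 and 12 months. Fewer features will be flagged, and power is modest at N = 24 to 30. If change scores were always intended, stating so is enough for Spearman; the Maaslin2 terms should still be written down.
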